### Study variables, blinding, and methods of assessment

The research team will be responsible for the screening and selection of eligible participants. Three team members will obtain written informed consent before study enrollment. Researchers will not be blinded to participant intervention. However, the researcher responsible for application of the MI technique and the one responsible for conducting conventional appointments will be blinded to the outcomes of the study. The participants will be blinded to group allocation and primary outcome. The investigators who are not outcome-blinded will be trained to obtained standardized anthropometric and BP measurements as well as to administer the study questionnaires.

### Clinical and sociodemographic variables

A structured questionnaire will be administered to all participants by a trained provider to collect clinical and sociodemographic data (age, sex, skin color, education, average household income, occupation, clinical co-morbidities, time since hypertension diagnosis, time followed at the outpatient clinic, current prescriptions, current BP [two isolated office measurements], heart rate, weight, height, and life habits).

### Anthropometric measurements

The anthropometric measurements of interest will be body weight, height, waist circumference (measured at the midpoint between the lowest rib and the superior edge of the iliac crest), and body mass index. All will be measured on the first and last protocol visits.

### Twenty-four-hour ambulatory blood pressure monitoring

ABPM will be conducted with periodically calibrated devices (DINAMAPA-2000, Cardio Systems Coml. Indl. Ltda.), with cuff size selected in accordance with the patient’s arm circumference. The protocol includes BP measurements every 15 min during the daytime (06:00 to 22:00) and every 30 min during the nighttime (22:00 to 06:00). ABPM will be considered satisfactory if at least 16 valid readings during the daytime and eight valid readings during the nighttime are obtained [18]. Participants will be evaluated by ABPM at the baseline and at the end of the follow-up (six months) in order to register BP during both sleep and wakefulness.

### Questionnaires and scales

The participants will answer the following questionnaires: Dietary Sodium Restriction Questionnaire (DSRQ) [25] for the assessment of sodium-restriction adherence; Self-Care of Hypertension Inventory – Brazilian Version (SC-HI) [26, 27] to measure self-care in hypertension patients; Medication Assessment Questionnaire [MAQ] [28] to evaluate adherence to drug therapy; International Physical Activity Questionnaire (IPAQ) [29] to quantify the level of physical activity; and the Epworth Sleepiness Scale (ESS) [30] to measure daytime sleepiness. All questionnaires will be administered at baseline and at the end of follow-up.

### Allocation

#### Intervention group

The scales and questionnaires defined in the study protocol will be administered at the first and last visits, as will ABPM. Since the first appointment, MI techniques will be used with the aim of working out the ambivalence involved in seeking treatment and modifying unhealthy behaviors, such as physical inactivity, unhealthy diet, tobacco use, alcoholic beverage intake, weight gain, stress, and non-adherence to pharmacological therapy. At all six face-to-face appointments, the MI approach will be applied with a focus on behavior change. Care will be provided in the MI style, which is characterized by being collaborative and non-coercive—for example, using open-ended questions, avoiding argumentation, and practicing empathy and reflective listening to encourage patients to talk about why, when, and how they might change the target behavior. The nurse will disclose the discrepancies that arise when the patient understand the differences between his current situation and his hopes for the future. In addition, the nurse will support self-efficacy to help the patient identify his skills and apply them in the context of hypertension. Finally, the nurse will also summarize what the patient wants to reach behaviorally. The guide which will be used during MI, based on the original methodology proposed by Miller and Rollnick, is shown in Table 1 [10–13, 22].

**Table 1 Tab1:** Guide for motivational interview appointment

Key points	
Acts by activating the patient’s own motivation for change and adherence to treatment	
Approach is patient-centered	
Collaborative spirit, evocative, and with respect for patient autonomy	
Allows exploring and solving ambivalence	
Offer critical resources that provide the space for a natural change	
Techniques	Skills
- Open questions	- Empathy
- Establish schedule with the patient	- Avoid arguments
- Reflective listening	- Talk about behavior change
- Request permission to inform	- Draw attention to discrepancies
- Stimulate the plan of action	- Respect autonomy
- Summarize the conversation	- Empower the patient
- Use evaluation scales	- Joint decision-making process
- Resist the reflex of repairing unhealthy behaviors	

The motivational interviewing counseling for each ambivalent behavior included the following steps:

(1) Assess the patient’s motivation and confidence on subjective scales of 1–10, to observe motivation to modify ambivalent behaviors and to evoke conversations about change

(2) Detect facilitators for changing these behaviors

(3) Elicit the “pros” and “cons” of any concerns

(4) Provide a menu of options to address any barriers or concerns about improving behaviors. The patient is asked about solutions for any barriers that present; if the patient does not present any barriers, the investigator encourages the patient to maintain their current behavior

(5) Assess the patient’s values and goals. This helps to create ambivalence between current behaviors and goals/values. Patients are asked to sort a list of values in terms of personal importance and to select around five that are most important. They are then asked to briefly discuss why the values/goals selected are important to them and then to explore what connection, if any, they see between their current health behavior and their ability to achieve these goals or live out these values

(6) Establish an action plan and make an overall summary of the appointment. The appointment, when appropriate, ends with an action plan to change the patient’s behavior, and the investigator summarizes what was talked and agreed upon and incorporates the patient’s suggestions and values

These strategies were reinforced during every monthly appointment

#### Control group

Patients allocated to the CG are expected to attend the same number of appointments as those in the IG: a total of six conventional (prescriptive) patients encounters, once monthly, with a nutritionist specializing in cardiology with no knowledge of the MI technique. During each CG appointment, patients will receive general recommendations for hypertension, such as increasing their intake of fruits and vegetables, reducing salt intake, avoiding processed and high-sodium foods, losing weight, and reducing their consumption of alcoholic beverages. Scales and questionnaires will be applied, as will ABPM at the first and last appointments, per protocol.

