In 2008, Ogedebbe et al. tested, in a randomized controlled trial (RCT), the effect of MI counseling versus usual care on medication adherence and BP in 190 African Americans with hypertension. The intervention group received standard care plus four sessions of MI at three-month intervals for a period of one year. The primary outcome was adherence to prescribed antihypertensive medication; the secondary outcomes were changes in office BP, self-efficacy, and intrinsic motivation at baseline and 12 months. The authors found no significant reductions in SBP between groups and no improvement in medication adherence in the intervention group [14]. More recently, in 2012, Ogedegbe et al. tested positive affection induction and self-affirmation strategies as a potential means of improving adherence to drug therapy by African American patients with hypertension. Their results suggested that this intervention was more effective in improving adherence to antihypertensive drug therapy compared with patient education alone [15]. In 2016, Boutin-Foster et al. assessed the effect on BP control of a combination of positive affection and self-affirmation strategies (including MI) compared with conventional educational measures in hypertensive African American patients over a one-year period, with bi-monthly telephone follow-up. This study had several limitations, e.g. at baseline patients in the intervention and control groups both received an educational workbook with the etiology of hypertension, treatment options, and lifestyle changes that one could make to improve BP control and to support goalsetting, and the same research assistants led appointments in the intervention and control groups. The results were not positive for a reduction in BP [16].

In the context of other chronic co-morbidities, Creber et al. compared MI versus usual care in patients with heart failure. The intervention consisted of one home-based motivational interview and three or four follow-up calls. The authors reported improvement of self-care in the MI group [17].

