The few existing studies carried out using this intervention showed limited effects on BP lowering with the MI approach. However, some results obtained to date were difficult to generalize because they were tested in a specific population (hypertensive African Americans); other studies used a combination of MI and other strategies; in others, interventions were not face-to-face. Furthermore, none used 24-h ambulatory blood pressure monitoring (ABPM) to measure BP; ABPM findings are now known to be associated more strongly with cardiovascular outcomes than office measurements [18, 19]. We designed this RCT to compare the effectiveness of MI versus usual care in reducing SBP and DBP, measured by ABPM, in patients with hypertension. The intervention will consist of an exclusive MI approach applied monthly in face-to-face appointments over a six-month follow-up period.

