## Methods/Design

### Study design

The “effect of MotIvational iNterviewing In HyperTensive patients” (MIdNIgHT) study is a randomized, single-center, parallel clinical trial with a follow-up period of six months. Patients with hypertension will be enrolled from Hospital de Clínicas de Porto Alegre (HCPA), a center in southern Brazil, and invited by telephone to participate in the trial. After a baseline evaluation, participants will be randomly allocated into two groups: (1) an MI intervention group (IG); and (2) a control group (CG) to receive usual care. MI sessions and standard clinical assessments (usual care) will be conducted face-to-face once monthly for six months. Anthropometric measurements, questionnaires and scales (Self-Care of Hypertension Inventory [SC-HI], Medication Assessment Questionnaire [MAQ], Dietary Sodium Restriction Questionnaire [DSRQ], International Physical Activity Questionnaire [IPAQ], Epworth Sleepiness Scale [ESS]), and ABPM will be performed at baseline and at the end of follow-up.

A flow diagram of the study design is presented in Fig. 1. The study timeline and schedule of enrollment, interventions, and assessments (Standard Protocol Items: Recommendations for Interventional Trials [SPIRIT] figure) and the SPIRIT Checklist are provided as Fig. 2 and Additional file 1, respectively.

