### Inclusion and exclusion criteria

The study will include female and male adults (aged 18–80 years) who have been receiving treatment and follow-up at the HCPA outpatient hypertension clinic for > 6 months. Patients must be on at least two antihypertensive medicaments at the time of recruitment and must not have been seen by a nutritionist or followed nutritional guidance in the last six months.

The exclusion criteria will be: pregnancy or lactation; gastrointestinal tract disease; inflammatory disease; chemotherapy; diagnosed diabetes; incapacity to engage in an interview due to intellectual disability or dementia, defined by application of a cognitive deficit assessment questionnaire [20]; and/or incapacity to participate in the intervention program without the need for third-party involvement.

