### Outpatient hypertension clinic and staff approach

The HCPA outpatient hypertension clinic is a multidisciplinary clinic attended by approximately 150 hypertensive patients per month. The clinic provides regular monitoring to optimize and encourage adherence to drug therapy and management of hypertension-related co-morbidities. Appointments are led by specialized cardiologists, pharmacists, psychologists, researchers, and graduate students.

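### The comparator is labelled usual care but is six monthly nutritionist counselling visits, so the objective and conclusion should be limited to that contrast

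*Protocol article*

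**What the plan says.** The Background closes with the objective: "We designed this RCT to compare the effectiveness of MI versus usual care in reducing SBP and DBP". Study design repeats the label, describing "a control group (CG) to receive usual care", and calls the control visits standard clinical assessments, held face-to-face once a month for six months.

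The Control group section says what those visits are: "a total of six conventional (prescriptive) patients encounters, once monthly, with a nutritionist specializing in cardiology with no knowledge of the MI technique". At each one the patient receives general advice on diet, salt, processed food, weight and alcohol. Under Study protocol, both arms attend six prearranged monthly appointments at the hospital's Clinical Research Center.

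Inclusion and exclusion criteria admit patients followed at the hypertension clinic for more than six months who "must not have been seen by a nutritionist or followed nutritional guidance in the last six months". The section on the clinic and its staff says: "Appointments are led by specialized cardiologists, pharmacists, psychologists, researchers, and graduate students".

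Under Lead researcher training, a specialist cardiovascular nurse delivers MI. The Abstract calls the control visits traditional appointments, and the Discussion contrasts MI with the traditional, prescriptive model of outpatient care.

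**The concern.** The label and the content of the control arm do not match. A reader of the objective would take usual care to mean what these patients would ordinarily get at the clinic. The Control group section describes a new monthly counselling programme with a professional whom none of them has seen in the preceding six months.

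What is at stake is the reading of the result. The counselling addresses diet, weight and alcohol, which MI also targets, and it overlaps with two secondary outcomes (low-sodium adherence and weight). If it lowers blood pressure, that fall comes off the between-group difference. A null result could then mean that both arms improved, yet under the stated objective it would be reported as no benefit of MI over usual care.

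**Working it through.** No disputed figure decides this point, so the check sets the sections side by side.

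**1. Recent care of an eligible patient.** Two entry conditions apply together: clinic follow-up longer than six months, and no nutritionist visit or nutritional guidance in the last six months. The last six months therefore lie wholly within clinic follow-up. Nutritionist contacts in that window: 0.

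**2. Care in the control arm.** One nutritionist contact a month, six in total over the six-month trial. Nutritionist contacts: 6.

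**3. Comparison.** 0 contacts in the six months before entry against 6 in the six months after. The staff list is consistent with this, since it names no nutritionist, but step 1 does not depend on it. No section says that monthly nutritionist visits are part of the clinic's routine.

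**4. What the trial estimates.** Let A be mean change in 24-h systolic pressure under nurse-delivered MI, B under the nutritionist visits, and U under usual clinic care. Then

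A − U = (A − B) + (B − U).

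The two arms give A − B. The objective names A − U. The missing term, B − U, cannot be estimated because no arm receives U, and the article gives no value for it. A − B equals A − U only if the counselling has no effect on blood pressure.

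**5. What else differs.** A and B differ in technique and also in the provider's profession (nurse against nutritionist). Even the contrast that is estimated is of two packages, not of MI technique alone.

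**6. Does the sample size depend on the label?** Inputs from the Sample size section: difference 8 mmHg between groups, SD 14 mmHg, power 80%, alpha 0.05 (taken as two-sided).

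n per arm = 2 × (1.960 + 0.842)² × 14² / 8² = 2 × 7.85 × 3.0625 ≈ 48.1, rounded up to 49.

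The t-test solution is 49.05, rounded up to 50. The stated 50 per arm, 100 in all before attrition, reproduces. The 8 mmHg is stated as a difference between the groups as designed, so the label does not disturb this calculation.

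**The case against.** The strongest reply is that the comparator is disclosed and well chosen. The Control group section gives provider, number, frequency and content. The Abstract and Discussion speak of traditional or prescriptive care. Matching the number of visits controls for contact, and added counselling in the control arm would more probably shrink than inflate a favourable MI result. All of this stands. It defends the arm but not the name: the words traditional and prescriptive describe a style, and do not tell a reader of the objective that controls start a new monthly programme.

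A second reply is that care before entry does not prove what would have followed. The clinic is described as multidisciplinary, and its staff list does not show that nutritional care is unavailable. This also stands, so the point should be put as care these patients had not recently been receiving.

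Four stronger readings are tempting but unsupported:

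- *The trial is underpowered because of the control arm.* This requires treating the planned 8 mmHg as an effect over care without a nutritionist and then subtracting a counselling effect. The article gives neither premise.
- *The entry rule was meant to keep nutritional counselling out of the trial.* No reason is given for the rule. It works equally well as a washout, so that both arms start without recent dietary advice.
- *The authors repeat a fault they criticise in an earlier trial.* The Background's complaint was that both arms received the same workbook and that the same research assistants led both. Here the prescriptive sessions go to one arm, under a separate provider.
- *Controls receive a known number of hours of counselling.* The 30 minutes is an average for the whole appointment, and the first and last visits also include questionnaires, measurements and placement of the ambulatory monitor.

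**Conclusion.** The mislabelling is real and follows from the document alone. The objective and Study design name usual care. The control arm is six nutritionist counselling visits, against none in the six months before entry. The trial estimates nurse-delivered MI against nutritionist-delivered prescriptive counselling matched for number of visits.

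The size in mmHg cannot be given, because it equals the unreported effect of the counselling over usual clinic care. The direction can be stated conditionally: if the counselling lowers blood pressure, the trial's difference understates the effect of MI over usual care. The main hazard is therefore a misread null result.

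The point assumes that the entry criteria are applied as written and that monthly nutritionist visits are not routine at this clinic, which no section contradicts. It corrects a label and an inference. A reader might infer a design flaw, but the documents do not support that: an active control with matched visits is a sound choice.

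**What to change.** - In the Background objective and in Study design, and wherever the conclusion is stated, replace usual care with *monthly prescriptive counselling by a nutritionist (active control matched for number of visits)*. Remove the equation of these visits with standard clinical assessments.
- State that provider profession also differs between arms: a nurse delivers MI and a nutritionist delivers the control visits.
- Limit the conclusion to that contrast, and say that a null result does not show that MI has no effect over usual clinic care.
- Report the change in 24-h systolic pressure within each arm, with its confidence interval, beside the between-group difference. Mark it as descriptive. It makes a fall in the control arm visible, but it does not estimate the counselling effect, since time trends and regression to the mean are included in it.

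The control arm, sample size and data collection stay as they are. The cost is some rewording, one descriptive table and a narrower claim. The article reports 50 patients included and seven completed, so the change could be made well before the full results are known.

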### Outcomes of interest

The primary outcome of the study will be a reduction of at least 8 mmHg in SBP and changes in DBP and mean BP. These outcomes will be measured by 24-h ABPM at the first and last protocol visits.

Secondary outcomes will include improvement of adherence to a low-sodium diet, adherence to self-care behaviors, regular use of antihypertensive medications, increase or maintenance of physical activity, weight reduction, evaluation of changes in daytime sleepiness, and cessation of smoking. These outcomes will be measured by the aforementioned questionnaires and scales at the first and last protocol visits.

### Statistical analysis

Continuous variables will be expressed as mean ± standard deviation or median and interquartile range. Categorical variables will be expressed as percentage or proportion. The chi-square test will be used for associations between sociodemographic and clinical variables with SC-HI scores. Student’s t-test or the Mann–Whitney *U* test, depending on data distribution, will be used for between-group comparison of quantitative variables. SBP and DBP measurements obtained during the study, as well as SC-HI scores, will be analyzed by generalized estimating equations with Bonferroni correction. BP differences between groups during treatment will be analyzed by repeated-measures analysis of variance (ANOVA). Analysis of covariance (ANCOVA) will be conducted to adjust possible differences regarding baseline measurements, as well as some risk factors and confounding factors when necessary. The 5% level of significance will be adopted and data will be analyzed in IBM SPSS Statistics for Windows, Version 20.0 (IBM Corp., Armonk, NY, USA).

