### Sample size

The sample size was calculated with WinPepi 11.20 software. Delta values of BP levels for the study population as reported by Correa et al. (4.4 mmHg for 24-h SBP and 2.7 mmHg for 24-h DBP) were used [24]. The sample size was estimated at 100 patients, 50 in the IG, and 50 in the CG, considering a difference in SBP of 8 mmHg between groups, a standard deviation of 14 mmHg, 80% power, and alpha = 0.05. To account for 20% attrition, the sample will consist of 120 patients, 60 in each group.

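### Chi-square is assigned to associations with SC-HI scores; it forces a score and several quantitative characteristics into categories and costs power in a descriptive side analysis

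*Protocol article*

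**What the plan says.** Three statements in the Statistical analysis section of the protocol article bear on this point.

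- Associations with patient characteristics: "The chi-square test will be used for associations between sociodemographic and clinical variables with SC-HI scores".
- Quantitative variables: a t-test or Mann–Whitney test "will be used for between-group comparison of quantitative variables". This sentence concerns group comparisons and does not name SC-HI.
- The same SC-HI scores again: "SBP and DBP measurements obtained during the study, as well as SC-HI scores, will be analyzed by generalized estimating equations", with a Bonferroni correction.

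The section Questionnaires and scales describes the SC-HI only as an instrument "to measure self-care in hypertension patients". The section Clinical and sociodemographic variables lists the characteristics. Some are categorical (sex, skin color, occupation). Others are measured quantities, among them age, household income, time since diagnosis, heart rate, weight and height.

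**The concern.** The plan names a specific test for a specific analysis, and the test does not suit the variables as the article describes them. Pearson's chi-square compares counts in categories. It uses neither the order of the scores nor the distance between them. Applied to a score, it needs the score to be cut first; applied to age or weight, it needs those cut as well. Each cut discards information.

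At stake is how well the trial can show which patient characteristics go with better or worse self-care. With 100 to 120 patients, moderate associations could easily be missed, and a non-significant chi-square could be misread as absence of association.

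**Working it through.** **The plan's own figure.** The article gives no calculation for SC-HI. Its one computed figure is the sample size: "The sample size was estimated at 100 patients, 50 in the IG, and 50 in the CG". The inputs named for it are a systolic difference of 8 mmHg, an SD of 14 mmHg, power of 80% and a 5% level. With n per group = 2(1.960 + 0.842)² × 14²/8² = 2 × 7.849 × 3.0625 = 48.07, this rounds up to 49; the t-based solution is 49.05, so 50 per group. The figure reproduces. It concerns systolic pressure and says nothing about power for the SC-HI associations.

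**Inputs.**
- From the article: 100 evaluable and 120 enrolled patients; "The 5% level of significance will be adopted" (taken as two-sided, which is an assumption).
- Assumed, because the article gives no SC-HI distribution: normal scores with equal spread, and a characteristic that splits the patients into two equal groups of n = 50 or n = 60. These groups are levels of a characteristic, not trial arms.
- Reference effect: the standardised difference d that a comparison of means would detect with 80% power, d = 2.802 × √(2/n). This is 0.560 for n = 50 and 0.511 for n = 60.

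**Step 1: score cut in two, then chi-square.** With p₁ and p₂ the proportions above the cut and p̄ their mean,

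power = Φ{ [ |p₂ − p₁| − 1.960 √(2p̄(1 − p̄)/n) ] / √([p₁(1 − p₁) + p₂(1 − p₂)]/n) }.

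For the median cut with n = 50: p₁ = 0.390, p₂ = 0.610, p̄ = 0.50. The numerator is 0.2205 − 1.960 × 0.100 = 0.0245, the denominator is 0.0975, the ratio is 0.25, and power is 0.60.

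| Cut (share above) | p₁, p₂ (n = 50) | Power, n = 50 | Power, n = 60 | n per group to regain 80% at d = 0.560 |
|---|---|---|---|---|
| none (means compared) | – | 0.80 | 0.80 | 50 |
| 50% | 0.390, 0.610 | 0.600 | 0.601 | 80 |
| 30% | 0.205, 0.395 | 0.550 | 0.553 | 90 |
| 20% | 0.124, 0.276 | 0.475 | 0.480 | 108 |

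The large-sample relative efficiency of a cut at quantile q, φ(z)²/[q(1 − q)], agrees: 0.64, 0.58 and 0.49. None of these values depends on when the cut was chosen.

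A second set of assumptions gives a similar result. With 60 per group, means 60 and 69, SD 18 and a cut at 70, power was 77% for the t-test and 57% for chi-square in 4,000 simulated datasets.

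**Step 2: the characteristic is cut too.** For a jointly normal score and characteristic, two median cuts multiply the efficiencies: 0.637 × 0.637 = 0.405. Then 2.802 × √0.405 = 1.783, and 1.783 − 1.960 = −0.177, which corresponds to power of about 43% where a correlation would have 80%. This is a large-sample approximation.

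**Step 3: score left uncut.** In 3,000 simulated datasets per setting (mean 65, SD 15, range 0–100, same d), chi-square was applied to the table of distinct score values.

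| Score step | Expected counts below 5 (no true difference) | Type I error | Power | t-test power |
|---|---|---|---|---|
| 1 point | over 99.9% | 0.2–0.3% | 1–2% | 79–80% |
| 3.33 points | 81–89% | 2.3% | 13–16% | 79–80% |

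The test errs on the conservative side and has little power. It does not inflate false positives.

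**The case against.** The strongest reply is that the authors distinguish continuous from categorical variables in the same paragraph, so they probably mean SC-HI in categories, with the threshold given in a fuller document. Reporting a score in categories in a descriptive table does not conflict with modelling it as a score elsewhere. No power is claimed for this analysis, and preferring regression may look like taste. The reading is plausible, but the loss in Step 1 remains, because it arises from the cut itself.

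Four stronger readings are tempting, and the article does not support them.

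- **That the test is invalid.** This needs a table of individual score values, which the article does not specify and which is unlikely to be meant. Even then the error is conservative, and its size depends heavily on the assumed score step.
- **That an unnamed cut allows associations to be picked afterwards.** A scoring threshold for a cited instrument is detail that an article may leave to the full protocol or analysis plan. Its absence here is no evidence that it is unspecified.
- **That the paragraph explicitly contradicts itself.** Besides the chi-square sentence, only the GEE sentence names SC-HI, and GEE can also fit binary outcomes. That the score is quantitative is a strong inference from the word scores and from the pairing with blood pressure, but the article does not say so.
- **That categorical outcomes such as smoking cessation are left without a test, since chi-square is mentioned only here.** That is condensation in an article and a different matter.

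**Conclusion.** The point holds as a minor one: a stated test suits its variables badly. Cutting the score lowers power from about 80% to about 48–60%, depending on the cut, whether or not the cut is prespecified; cutting a quantitative characteristic as well lowers it further. These figures rest on normal scores, two equal groups, 100 to 120 patients and an effect of 0.51 to 0.56 SD. The article supplies only the patient numbers and the significance level.

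The consequence is limited. The associations are not among the primary or secondary outcomes listed under Outcomes of interest. The ambulatory blood pressure outcome and the comparison of SC-HI between trial groups, which uses GEE, are unaffected.

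**What to change.** Replace the chi-square sentence with one that keeps SC-HI as a quantitative score: a t-test, ANOVA or rank test for categorical characteristics, and Pearson or Spearman correlation or linear regression for quantitative ones, labelled exploratory. Keep chi-square for pairs of variables that are truly categorical. If a clinically meaningful SC-HI category is wanted as well, state it in advance and limit chi-square to categorical characteristics against that category, as a supplement to the score analysis.

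The cost is one sentence. No extra data or patients are needed, and the named software covers these methods. The article reports that recruitment was still under way, so the change could be made before analysis.
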